## **Definition of Analysis Populations**

The analysis population is intent-to-treat (ITT). All participants in the randomised groups are analysed. In addition, a complier-average causal effect analysis (CACE) will be conducted to test any influence of compliance on the intent-to-treat intervention effect of the primary trial objectives/ analyses. CACE is then compared with the intent-to-treat intervention effects resulting from the primary analyses and results are reported.

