In case of any significant interaction effects between time and baseline moderators, simple slope analyses are carried out to investigate the direction of any moderation effects.

Further tertiary trial objectives to investigate whether changes (decrease) in process measures, such as rumination, intrusive memories, and increases in concrete thinking, from baseline to post-intervention in the iCT-R condition predict lack of PTSD or MDD diagnoses

[name], [name], [name], [name], [name], [name], [name], [name], [name], [name], [name], & [name] Cognitive resilience training to prevent PTSD and MDD in paramedics: A randomised controlled trial.

(versus presence of PTSD or MDD diagnoses) at 1-year follow-up are analysed using logistic regressions with difference scores from pre to post for the process measures and baseline scores of PTSD or MDD symptom severity as covariate.

CACE analysis:

A complier-average causal effect analysis (CACE) is used to test the influence of compliance on the intent-to-treat intervention effect of the primary trial objectives/ analyses. Magnitude of compliance will be defined as 1) number of online modules completed during the intervention, and 2) practice of tools. Based on these variables, trajectories of compliance are determined. CACE will then be compared with the intent-to-treat intervention effects resulting from the primary analyses and the results will be reported.

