### **Supplementary/ Additional Analyses and Outcomes**

Additional exploratory analyses due to the Covid pandemic, suggestions taken from [FDA](#) guidelines (June 2020) [22] and Mayer et al. (2020) [23] and adapted to the needs of the current trial:

The trial took place before and during the outbreak of the Covid pandemic. Additional reporting of descriptive statistics and missing data, additional exploratory analyses, and sensitivity analyses are needed to capture any possible impact of the pandemic on the main trial objectives.

Two Covid periods (pre-Covid/ before March 2020, which marks the first UK national lockdown, or possibly after-Covid, coded as ‘0’, and during-Covid, since March 16, 2020, coded as ‘1’) are defined. For each participant at each assessment time point it will be classified whether the assessment took place before or after Covid impact versus during Covid impact. This way exogeneous time-varying covariates are generated for further analyses.

Additionally, a COVID questionnaire was implemented to capture any possible subjective impact by COVID reported by the participants on outcome.

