Additional missing data explorations are reported. Any missing data, withdrawal from the intervention, or loss to follow-up are reported in tables for the whole sample and by intervention groups based on the Covid status variables for the short-term primary outcome time point 1-year follow-up and the 2-year follow-up assessment point, once completed (means and standard deviations for continuous outcomes, absolute numbers and percentages for dichotomous outcomes).

In the case of any missing data, withdrawal, or loss to follow-up dependent on Covid status or the endorsement of the COVID questions, additional sensitivity analyses need to be carried out.

CACE analyses:

In the case of potential intervention heterogeneity due to any influence of the Covid pandemic, additional CACE analyses are carried out, as well, to test whether Covid status or questions had an influence on compliance to the interventions. In case of any differences the Covid CACE is compared with the intent-to-treat intervention effects resulting from the primary trial analyses and results are reported.

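### The SAP gives the question of whether Covid influenced compliance to a CACE analysis, which estimates the training effect among compliers; no planned model has compliance as its outcome

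*Combined protocol and SAP*

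**What the plan says.** The sentence at issue is in the SAP under Supplementary/Additional Analyses and Outcomes, in the Covid paragraph headed CACE analyses. It has three parts.

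- The trigger: "In the case of potential intervention heterogeneity due to any influence of the Covid pandemic".
- The purpose: "additional CACE analyses are carried out, as well, to test whether Covid status or questions had an influence on compliance to the interventions".
- The follow-on, if there are differences: "the Covid CACE is compared with the intent-to-treat intervention effects resulting from the primary trial analyses".

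Under Definition of Analysis Populations the SAP describes CACE in the opposite direction: a "complier-average causal effect analysis (CACE) will be conducted to test any influence of compliance on the intent-to-treat intervention effect". The sections on compliance and on analysis methods repeat that direction.

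Compliance has two components: "Magnitude of compliance will be defined as 1) number of online modules completed during the intervention, and 2) practice of tools". The SAP adds: "Based on these variables, trajectories of compliance are determined". It gives no cut-off for a complier, no estimator, and no model linking Covid to either component.

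The Covid variable is attached to visits: "For each participant at each assessment time point it will be classified whether the assessment took place before or after Covid impact versus during Covid". A COVID questionnaire score is planned as a second covariate. The nearest planned output on compliance is a set of descriptive tables of missing data, withdrawal from the intervention and loss to follow-up by Covid status.

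**The concern.** The stated question has compliance as its outcome: did the pandemic change how much training participants did? CACE has diagnosis or symptoms as its outcome, and compliance enters as an input. A CACE contrast between Covid periods asks whether training worked differently among compliers. Setting CACE beside the ITT effect shows how far non-compliance dilutes the effect. Neither is a test of Covid on compliance.

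The trial could therefore make a statement about Covid and uptake from a statistic that does not bear on it. The trigger adds a second gap: a change in compliance that does not show up as heterogeneity of the intervention effect would not be examined at all.

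**Working it through.** **The plan's own figure.** The inputs, from the protocol's section on the number of participants, are a 25% risk without intervention (subsyndromal cases included), a 50% relative reduction to 12.5%, 80% power and alpha 0.05. The SAP makes the test two-sided.

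- OR = (0.125/0.875)/(0.25/0.75) = 0.429.
- n per arm = [1.96·√(2·0.1875·0.8125) + 0.8416·√(0.25·0.75 + 0.125·0.875)]² / 0.125² = 151.9, so 152.
- 2 × 152 = 304; 3 × 152 = 456; 456/0.8 = 570, or 190 per arm.

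The stated sample size reproduces exactly. The point does not depend on it, but it supplies the control risk and arm size used below.

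**Why the contrast is uninformative.** Let compliance in Covid stratum v be c_v and the effect among compliers be δ in both strata. With no access to iCT-R in Standard Practice and no effect in non-compliers:

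- ITT_v = c_v × δ
- CACE_v = ITT_v / c_v = δ

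So CACE₁ − CACE₀ = 0 whatever c₀ and c₁ are.

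**Simulation.** iCT-R against Standard Practice, 190 per arm, half of each arm in the Covid stratum, control risk 25%, two-sided 5%, 20,000 trials per row. CACE is the risk difference divided by compliance, with a delta-method standard error. The direct test compares compliance between Covid strata within iCT-R.

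| Compliance (non-Covid/Covid) | Complier effect (non-Covid/Covid) | CACE by Covid rejects | Direct test rejects | ITT-by-Covid rejects |
|---|---|---|---|---|
| 70% / 70% | −0.15 / −0.15 | 4.8% | 5.2–5.3% | 5.1% |
| 80% / 50% | −0.15 / −0.15 | 4.8% | 99.5% | 8.8% |
| 90% / 40% | −0.15 / −0.15 | 4.5% | 100% | 15.4% |
| 70% / 70% | −0.20 / 0 | 39.8% | 5.2% | 39.7% |
| 70% / 70% | −0.25 / +0.10 | 84.0% | 5.2% | 83.7% |
| 80% / 50% | −0.125 / −0.20 | 8.6% | 99.4% | 5.1% |

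Rows 2 and 3 change only compliance, and the CACE contrast stays at its nominal level. Rows 4 and 5 change only the training effect, and it rejects. In row 6 both change, so that the ITT effects are equal (0.8 × 0.125 = 0.5 × 0.20 = 0.10). CACE then rejects slightly more often, but because the complier effects differ. At 2,000 per arm the CACE contrast still rejects only 5.1% in row 2, so sample size does not help.

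**CACE against ITT.** With no Covid effect anywhere, CACE = ITT/c. An ITT difference of 0.25 − 0.125 = 0.125 becomes:

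- 0.125/0.5 = 0.250 at 50% compliance
- 0.125/0.7 = 0.179 at 70%
- 0.125/0.9 = 0.139 at 90%

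Nor does the gap show how compliance is spread over Covid periods. Take δ = −0.15 and an even split. Compliance of 80%/50% gives an overall ITT of −0.15 × 0.65 = −0.0975 beside a CACE of −0.15. Compliance of 65% in both periods gives the same pair.

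**The trigger.** The SAP takes significant Covid interactions as a possible sign of heterogeneity. On that reading, the last column shows how often rows 2 and 3 would reach the Covid CACE: 8.8% and 15.4%. The compliance change would go unexamined in 91.2% and 84.6% of trials.

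**Timing.** Modules belong to the six-week training period, so Covid status at a 1- or 2-year visit cannot have influenced them. Tool practice is different. The protocol's schedule of procedures collects it at 6, 24, 52 and 104 weeks, so visit-level Covid status suits it.

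**The case against.** The strongest reply is that the SAP names no CACE estimator. Trajectories of compliance suggest that compliance will be modelled, and a latent-class CACE can carry a compliance submodel with Covid as a predictor. The follow-on clause can also be read as two steps: look for compliance differences, then compare effects. This stands so far as it goes. It would be too strong to say that no analysis called CACE could answer the question. But the submodel, not the CACE, would then be the test, and none is specified. Under the two-step reading, the first step has no model.

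A charitable reading is that the authors want to know whether compliance explains Covid heterogeneity in the effect. That is a reasonable question, but not the one the sentence states.

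Two stronger readings are tempting and are not supported:

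- A reader might infer that an effective programme would by itself produce a false Covid finding, because CACE would differ from zero. The SAP never says a non-zero CACE would be taken as a Covid effect on compliance, and rejecting CACE = 0 under the design effect mostly restates the planned 80% power.
- A reader might infer that visit-level Covid coding makes the whole exercise meaningless. The mismatch concerns modules only. Even there, status at the 6-week visit partly marks exposure during training.

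It is also fair that withdrawal from the intervention is tabulated by Covid status without the trigger, so compliance loss would not be wholly invisible. Those tables are descriptive and do not cover modules completed or tool practice.

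**Conclusion.** The point holds. The SAP assigns an exploratory question about compliance to an analysis that, by its own description, targets the intervention effect. When only compliance differs and the complier effect is constant, a CACE contrast by Covid status rejects at about 5% at any sample size. The CACE-to-ITT comparison shows a gap under incomplete compliance even with no Covid effect.

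The compliance rates (40–90%), complier effects, even Covid split, exclusion restriction and absence of iCT-R access in Standard Practice are assumptions. The null behaviour of the contrast does not depend on the particular rates or split. The power of the direct test does, and 99.5% is not a forecast for modules. If every 1-year visit was complete by the SAP date of 21 April 2021, randomisation ended by about 22 April 2020 (364 days earlier). Training reached 16 March 2020 only for those randomised from about 3 February 2020 (42 days earlier). The planned trial end of 30 January 2021 with 104-week follow-up would imply that nobody trained during Covid. The documents do not give recruitment dates.

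The analysis is exploratory and no primary estimate or test depends on it. The change is worth making because it is cheap and the present sentence does not deliver what it promises.

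**What to change.** Replace the sentence with a direct exploratory analysis in iCT-R and Mind-Online, run regardless of the heterogeneity result:

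1. Modules completed, regressed on whether the six-week training period overlapped 16 March 2020 or later, arm, and their interaction. State first how many participants overlapped.
2. Practice of tools at 6, 24, 52 and 104 weeks, regressed on Covid status at that visit, arm, and their interaction. Include visit as a factor and a participant random effect, since later visits are more likely to fall in the Covid period.
3. The COVID questionnaire score as an alternative predictor of practice, at visits where it is available.

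Report estimates with 95% confidence intervals. Keep CACE only for the intervention effect among compliers, and drop its comparison with ITT as evidence on this question.

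The cost is a wording change and a little extra exploratory analysis of data the trial already collects. The modules estimate may be imprecise, or not estimable, if few or none trained after 16 March 2020; the count and interval will show this.

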## **Harms**

No adverse events are anticipated. The procedure for adverse events (AE) and serious adverse events (SAE) are reported in the trial protocol paper.

[name], [name], [name], [name], [name], [name], [name], [name], [name], [name], [name], & [name] Cognitive resilience training to prevent PTSD and MDD in paramedics: A randomised controlled trial.

The total number of serious adverse events (SAE) and the number of SAE per participant (if at least one SAE) are reported in each randomised intervention group. If there is at least one SAE, a comparison between the intervention groups regarding the total number of SAE and the number of SAE per participant is made. The safety analysis is also ITT. Results of these comparisons, such as statistical tests and ratios, are reported.

No additional safety analyses are needed due to the Covid pandemic as the continuation of the trial during the pandemic did not put participants at a higher risk.

#### **Health Economics and Cost Effectiveness**

Health economic analyses (intervention costs per QALY gained) will be conducted by [name] and are therefore not part of this analysis plan.

#### **Meta-analyses (if applicable)**

No meta-analyses are planned.

#### **SPECIFICATION OF STATISTICAL PACKAGES**

All analyses will be done in RStudio [24]. The main trial objectives are analysed using the R packages *lme4* [25] and *nlme* [26].

[name], [name], [name], [name], [name], [name], [name], [name], [name], [name], [name], & [name] Cognitive resilience training to prevent PTSD and MDD in paramedics: A randomised controlled trial.

